### Other variables of interest

#### Treatment evaluation

The 8-item Client Satisfaction Questionnaire (CSQ-8) [92] will be administered to assess patient satisfaction with treatment in both the experimental group and the control group. The CSQ has high internal consistency (α = .93) [93].

In addition, the 10-item System Usability Scale (SUS) [94] will be administered to participants receiving TAU + iERT, after they have finished iERT-treatment regularly or prematurely. The SUS assesses participants’ subjective perception of the usability of a technology system. The questionnaire will be administered once to each iERT-therapist as well. The SUS has been demonstrated to be reliable and robust [95].

#### Contextual information of victimization

The Safety Monitor assesses contextual information about the most recent incident of each violent crime experienced in the past 12 months: where the incident took place, whether the participant knew the perpetrator and what their relationship was, and whether the participant reported the crime to the police. To obtain more detailed information on the most recent victimization incident, we extended the Safety Monitor with supplemental questions, such as: “did you use substances or alcohol prior to the incident?”.

#### Victimization of non-violent crimes

Apart from violent crimes, we will ask participants whether and how frequently they have experienced the following non-violent crimes in the past 12 months: burglary, car theft or theft of another motor vehicle, pickpocketing or non-violent robbery, theft of other property, fraud, and vandalism.

#### Perpetration

Perpetration will be measured with the extended version of the Safety Monitor. For each violent crime, participants will be asked whether they have ever committed that crime. If so, participants are asked whether and how frequently they have permitted that crime in the past 12 months. For each crime they committed in the past 12 months, they will be asked whether they simultaneously were both victim and perpetrator, and if so, whether they committed the crime in self-defense. Prior to these questions, participants are reminded about the confidentiality of the assessment.

#### Safety perception and perceived controllability of victimization

Section 3 of the Safety Monitor assesses safety perception by asking participants whether and how often they feel unsafe. We extended this section with four questions regarding safety perception and perceived controllability of victimization, such as: “To what extent do you consider yourself able to prevent ending up in hazardous situations?” and “How likely do you think it is that you will fall victim to each of the following during the next twelve months?”.

### Data analysis

#### Effectiveness

Primary data analyses will be conducted in conformity with the intention-to-treat paradigm. In addition, per-protocol analyses will be performed. Missing data will be addressed using multiple imputation. Treatment effect regarding the primary outcome measure will be modeled with Generalized Linear Mixed Models (GLMM) with a Poisson distribution, since the primary outcome measure consists of count data. Treatment effect concerning the secondary outcome variables will be modeled using GLMM as well, taking into account distributional characteristics of the data. Considering the expected skewness of the data, we assume that removal of outliers will be necessary.

To assess the magnitude of treatment effects on primary and secondary outcome measures, Cohen’s d between groups effect sizes for each time point will be calculated. Effect sizes of d = .9 are considered large, effect sizes of d = .45 are considered moderate and effect sizes of d = .15 are considered small [96]. Furthermore, multilevel mediation models will be used to examine various potential treatment mediators. Although the major question of this study concerns victimization, we will determine differences between both conditions regarding response and remission rates of depression as well.

#### Cost-effectiveness

The economic evaluation will be conducted alongside the randomized controlled trial and will be performed according to the intention-to-treat principle. With regard to the economic evaluation, we will take into account the CHEERS statement [97] and the 2015 ISPOR good research practices task force report on cost-effectiveness analysis alongside clinical trials [98]. Using a societal perspective, we will evaluate the relationship between costs – direct medical costs, participant costs and productivity losses, as measured with the TiC-P – and health outcomes of TAU + iERT and TAU alone at 12 months after baseline.

We will take into account four types of costs: (1) the costs of offering the intervention (TAU + iERT or TAU only); (2) costs stemming from general health care uptake besides TAU + iERT or TAU only, including the costs of medication; (3) patients’ out-of-pocket expenses (e.g. travel costs, leisure time spent on receiving care); and (4) costs stemming from productivity losses due to absenteeism or reduced efficiency while at work (presenteeism). Health care costs will be valued based on standard cost prices reported in the Dutch guideline for economic evaluation [99]. Costs due to productivity losses will be based on the gender- and age-specific labor costs. Data on resource use (health care uptake) and productivity losses will be collected with the widely-used TiC-P [64]. Using this approach, cumulative costs over the full trial period will be obtained from the cost estimates at times of the data collection waves.

We will perform both a cost-effectiveness analysis with incidents of victimization as effect measure and a cost-utility analysis using QALYs. QALYs will be based on preferences from general population samples to derive value sets to calculate the EQ-5D-5 L health utilities for the Netherlands. Using the area under the curve (AUC) method, the periods between the measurement waves will be multiplied by the utility of the health state in that period. This allows for the computation of quality adjusted life years (QALYs) over the entire trial period.

Incremental cost-effectiveness ratios (ICERs) and cost-effectiveness acceptability curves (CEAC’s) will be calculated. To estimate the uncertainty around the ICERs, 5000 bootstrapped samples will be extracted and plotted on cost-effectiveness planes. These data will also be used to plot Cost Effectiveness Acceptability Curves (CEACs). One-way sensitivity analyses and/or scenario analyses directed at assessing the impact of uncertainty in the main cost drivers will be performed to gauge the robustness of our findings. In addition, a sensitivity analysis in which covariate-adjusted CEACs can be constructed will be conducted using net benefit regression methods [100, 101].

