**Methods:**

In a multicenter randomized controlled trial with parallel group design, patients with a major depressive disorder and a history of violent victimization over the past three years (*N* = 200) will be allocated to either TAU + iERT (*N* = 100) or TAU only (*N* = 100), based on computer-generated stratified block randomization. Assessments will take place at baseline, 8 weeks, 14 weeks, and 6 months after start of treatment, and 12, 24, and 36 months after baseline. The primary outcome measure is the total number of violent victimization incidents at 12 months after baseline, measured with the Safety Monitor: an adequate self-report questionnaire that assesses victimization over the preceding 12 months. Secondary outcome measures and mediators include emotion dysregulation and depressive symptomatology. An economic evaluation with the societal perspective will be performed alongside the trial.

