## Background

Psychiatric patients are at high risk of becoming victim of a violent crime [1, 2]. Prevalence rates of violent victimization – commonly defined as physical assault, sexual assault or threat of violence – in psychiatric patients worldwide have been demonstrated to be up to 11 times higher in comparison with the general population, with most studies reporting 3 to 6-fold elevated odds [1–3]. Recently, a Dutch prevalence study conducted by Kamperman et al. (2014) [3] showed that 19.1% of outpatients with severe mental illness (SMI) had become victim of a violent crime over the past year, as compared to 6.1% of the general population. Whilst research has focused mainly on psychiatric patients as perpetrators (e.g., [4]), several studies have demonstrated that patients are more likely to be victim rather than perpetrator of a crime [5, 6].

Victimization is a highly stressful event that can aggravate existing symptoms [7] and substantially decrease quality of life [8] in psychiatric patients. Victimization is associated with physical injury, hospitalization [7, 8], treatment resistance [9], depression, posttraumatic stress disorder, and substance abuse [7]. Furthermore, initial victimization heightens the risk of future revictimization [10, 11], and therefore might induce a vicious cycle of stressful experiences and worsening symptoms. Due to increased service use, health care use, and productivity losses, victimization has a substantial economic impact as well [12].

To date, most studies have addressed victimization in patients with severe mental illness (SMI) [6, 13, 14] and patients with substance use disorders [15, 16]. Studies that specifically address victimization in other psychiatric populations, such as outpatients with affective disorders, are scarce. The only clinical study that focused on patients with depression revealed that depressed outpatients were 3.4 times more likely to be victim of a violent crime than members of the general population [17]. In a general population study of women, a current depression predicted subsequent physical victimization, but not subsequent sexual victimization [18]. Furthermore, a meta-analysis demonstrated depressed subjects to be vulnerable to domestic violence [19].

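### The economic evaluation is labelled societal, but its closed cost list has no police or justice costs although the effect measure is violent crime, so a negative or borderline societal conclusion would not be supported

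*Protocol article*

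**What the plan says.** The perspective is stated twice. The abstract (Methods) says: "An economic evaluation with the societal perspective will be performed alongside the trial". The Cost-effectiveness section under Data analysis says "Using a societal perspective, we will evaluate the relationship between costs", and the same sentence specifies the costs meant: "direct medical costs, participant costs and productivity losses, as measured with the TiC-P".

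The section then gives a numbered list, introduced by "We will take into account four types of costs":

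1. delivering the treatment in either arm;
2. "costs stemming from general health care uptake besides TAU + iERT or TAU only, including the costs of medication";
3. what patients spend themselves, with travel and time given up for care as examples;
4. lost productivity, through absence or reduced performance at work.

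Two analyses use these costs at 12 months: cost per victimization incident and cost per QALY. The closing paragraph of the section plans one-way sensitivity or scenario analyses, aimed at uncertainty in the largest cost items. It names no further cost category.

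Two other sections bear on the point. Under Primary outcome measure, the Safety Monitor asks how often each of three crimes (physical assault, sexual assault, threat) occurred in the past 12 months. Under Contextual information of victimization, it asks "whether the participant reported the crime to the police", but only for the most recent incident of each crime. The protocol does not link that item to costing.

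**The concern.** In many mental health trials, leaving out police and justice costs changes little, because there is no reason for them to differ between arms. Here they arise from the events that the intervention is meant to prevent and that form the denominator of the cost-effectiveness ratio. If iERT reduces incidents, these costs fall in the iERT arm and the planned analysis does not see it.

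This is not a detail left to a fuller document. The article itself closes the list at four types and names the result societal. At stake is the reading of the economic result, which belongs to a stated aim of the trial (Research aims): a finding that iERT is not cost-effective for society, or only marginally so, could come from costs that were never counted.

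**Working it through.** **Scope check.** Each omitted cost is set against the list.

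- Police costs: not intervention, not health care, not paid by the patient, not productivity. Outside all four types.
- Justice costs: the same.
- Victim support: open. Part of it might be recorded as general health care uptake. The TiC-P items are not shown, so omission cannot be established.

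**Direction and size.** The plan states no figure to reproduce here. The inputs are:

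- expected incidents per patient over 12 months: 3.0 (Sample size);
- expected relative reduction: 30% (Sample size);
- c, the average police and justice cost per incident: not in the documents;
- dC, the incremental cost as the plan would measure it: not in the documents.

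Incidents averted per patient: dE = 0.30 x 3.0 = 0.9. Per 100 patients that is 300 against 210, or 90 averted.

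Incremental cost with the omitted item included: dC - c x dE = dC - 0.9c.

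Cost per incident averted: (dC - c x dE) / dE = dC/dE - c. The ratio falls by exactly c, whatever the size of the effect.

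Cost per QALY, with QALY gain dQ: (dC - 0.9c) / dQ. With a threshold L per QALY, iERT would be wrongly judged not cost-effective whenever L x dQ < dC < L x dQ + 0.9c. The band in which the conclusion changes is 0.9c wide.

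**Illustration.** Both c and dC = +EUR 500 are assumptions, chosen only to show how the result moves.

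| Assumed c (EUR) | Omitted saving per patient, 0.9c (EUR) | Cost per incident averted as planned (EUR) | With c included (EUR) |
|---|---|---|---|
| 100 | 90 | 556 | 456 |
| 500 | 450 | 556 | 56 |
| 1,000 | 900 | 556 | -444 |
| 5,000 | 4,500 | 556 | -4,444 |

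For example, at c = 1,000: (500 - 900) / 0.9 = -444. A negative value here means fewer incidents at lower cost.

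The average c depends on how many incidents reach the police. If unreported incidents cost the police and justice system nothing, c is the unit cost of a reported incident times the share reported. A unit cost of EUR 1,000 with one incident in ten reported gives c = EUR 100, the first row.

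**Sign.** With dE > 0 the omission works against iERT. A result already favourable to iERT becomes more favourable once c is included. If incidents were to rise in the iERT arm, the sign would reverse.

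**The case against.** The strongest reply is that this is a dispute over a label. The methods sentence that says societal also spells out the costs meant, and these go beyond a health care payer's view. Nothing in the document says that the word must cover police and justice, and the economic guidance that the protocol cites cannot be consulted here. That stands in part: no breach of that guidance can be asserted. The abstract, however, carries the label without the list. In this trial the missing costs also follow the effect measure itself, so the label invites a conclusion that the cost set cannot carry.

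Several stronger readings are tempting, and the documents do not support them.

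- *Any societal conclusion, favourable or not, would be unsupported.* If incidents fall, the bias is against iERT, so a favourable conclusion would still hold. Only a negative or borderline one is exposed.
- *The Background shows that the authors recognise police and justice costs and then drop them.* It says "Due to increased service use, health care use, and productivity losses, victimization has a substantial economic impact as well", but service use is not defined there and could mean other services.
- *Victim support is left out.* This is not shown, for the reason given in the scope check.
- *A particular sum is missing.* The documents contain no cost per incident. The outcome also counts threats without actual violence and unwanted touching, many of which may cost the police nothing. The 0.9 is itself a planning figure, and the protocol says that the effect size is hard to determine.
- *The trial already records police contact for costing.* Reporting is known only for the latest incident of each crime, so it cannot cost repeated incidents.

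One further objection stands. For cost per incident averted, including c shifts the ratio by a constant. A decision maker's value for an averted violent crime may already contain the justice savings, and subtracting them from costs as well would count them twice. The point is therefore clearest for cost per QALY.

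**Conclusion.** The point holds as a mismatch between the stated perspective and the costs counted, limited to police and justice costs. If iERT reduces incidents, the incremental cost is overstated by c x dE per patient, which is 0.9c on the protocol's planning assumptions of 3.0 incidents and a 30% reduction. The algebra is certain. The euro amount is unknown because c is not in the documents, and it could be small if few incidents are reported.

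The consequence runs one way: a negative or borderline conclusion called societal would not be supported, above all for cost per QALY, while a positive one would still hold. The effectiveness analyses are untouched. The change is worth making because cost-effectiveness is a declared aim and the correction is cheap.

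**What to change.** 1. In the abstract and in the Cost-effectiveness section, describe the base case by the costs it contains: health care including the intervention, patient and productivity costs.
2. Add one scenario to those already planned. Multiply the 12-month Safety Monitor counts for each of the three crimes by published police and justice unit costs. Vary these over a range that includes low reporting.
3. Add victim support to that scenario only if the TiC-P does not already capture it. Exclude intangible victim costs, which would be counted again beside incidents or QALYs.
4. State that any value placed on an averted incident must not already include justice savings.

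The cost is a change of wording and one further analysis, with no new data from participants. The downside is that unit costs and reporting rates must come from outside sources and are uncertain, and that the headline economic claim becomes narrower.

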During the treatment phase, assessments will be administered at 8 weeks, 14 weeks, and 6 months after start of TAU in both the experimental and the control group. Follow-up assessments will be administered at 12, 24, and 36 months after the first baseline assessment. Except for the MINI, which will be assessed in a telephone interview at 12 months after baseline, all assessments will be conducted online. Patients receive an e-mail with a link to the self-report questionnaires, and those who have not completed an assessment within 4 days will receive a reminder via e-mail. Patients who have not completed the assessments after one week will be approached via telephone by a research assistant. If necessary, online assessments can also be completed over the telephone by an assistant who is blinded to treatment condition. Participants will be compensated with a voucher of 15 euros per assessment for both the first and second part of T0, T1, T2, T3, T5 and T6, and a voucher of 30 euros for T4.

Additional questionnaires will be sent out in the TAU + iERT condition: a visual analogue mood scale (VAMS) is to be completed online after every iERT-session in the online treatment platform, and the System Usability Scale (SUS) and Technical Alliance Inventory (TAI) are to be filled out after completion of iERT. The SUS will also be sent out once to each iERT-therapist. Table 1 provides an overview of all instruments per assessment.

**Table 1 Tab1:** Overview of instruments per assessment

Instrument	T0_1_	T0_2_	T1	T2	T3	T4	T5	T6^a^
Mini International Neuropsychiatric Interview	x					x		
Safety Monitor	x					x	x	x
Inventory of Depressive Symptomatology	x		x	x	x	x	x	x
Difficulties in Emotion Regulation Scale	x		x	x	x	x	x	x
Visual Analogue Mood Scale	x		x^b^	x	x	x	x	x
Positive and Negative Affect Schedule	x		x	x	x	x		
Demographic questionnaire	x							
Posttraumatic Diagnostic Scale		x			x			
Childhood Trauma Questionnaire	x							
List of Threatening Experiences		x						
Brief Symptom Inventory		x			x			
Utrechts Coping List		x				x		
Ruminative Response Scale		x	x	x	x	x		
Pearlin Mastery Scale		x	x	x	x	x		
Dysfunctional Attitude Scale		x	x	x	x	x		
Self-Esteem Rating Scale	x							
Inventory of Interpersonal Problems		x				x		
NEO Five Factor Inventory			x					
EuroQol 5D-5 L	x				x	x		
Trimbos questionnaire on Costs associated with Psychiatric Illness	x				x	x		
Working Alliance Inventory				x				
Client Satisfaction Questionnaire				x				

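### Covariate adjustment appears only in a CEAC sensitivity analysis, which implies that the main incremental QALY and ICER are not adjusted for baseline EQ-5D utility

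*Protocol article*

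**What the plan says.** Under Data analysis, Cost-effectiveness, the protocol article sets the horizon by comparing costs with "health outcomes of TAU + iERT and TAU alone at 12 months after baseline". QALYs come from EQ-5D-5L utilities: "Using the area under the curve (AUC) method, the periods between the measurement waves will be multiplied by the utility of the health state" in each period.

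The main analysis is then described as follows: "Incremental cost-effectiveness ratios (ICERs) and cost-effectiveness acceptability curves (CEAC’s) will be calculated". On uncertainty: "To estimate the uncertainty around the ICERs, 5000 bootstrapped samples will be extracted and plotted on cost-effectiveness planes". The same bootstrap data supply the CEACs. No covariate is mentioned at any of these steps.

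Adjustment comes last: "In addition, a sensitivity analysis in which covariate-adjusted CEACs can be constructed will be conducted using net benefit regression methods". The covariates are not named.

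Three other places bear on the point:

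- Table 1 schedules the EQ-5D-5L at T0_1, T3 and T4, so a baseline utility exists for each patient.
- Randomization and procedure stratifies by mental health care site only.
- The same section times T1 to T3 from the start of treatment ("assessments will be administered at 8 weeks, 14 weeks, and 6 months after start of TAU"), whereas T4 is timed from baseline.

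**The concern.** Baseline utility enters a 12-month AUC in two ways. It is the first point on the curve, so it has a weight of its own. It also predicts the later utilities, because patients who start better tend to stay better. If the arms differ by chance at T0_1, part of that difference reappears as a QALY difference that treatment did not cause. Stratifying by site does not balance baseline utility.

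The article does not simply pass over adjustment. It raises the subject and gives it a secondary place: covariate-adjusted CEACs are an extra sensitivity analysis. This suggests that the main ICER, cost-effectiveness plane and CEAC are unadjusted.

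Cost-effectiveness is a named aim of the trial, and the sample size was set on incident counts rather than QALYs. Avoidable noise in the incremental QALY therefore matters to how much the economic evaluation can say.

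**Working it through.** The article gives no utility SD, correlation, expected QALY gain or economic sample size, so there is no stated figure to reproduce. The check shows the size of the mechanism under labelled assumptions.

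**Inputs from the article**
- EQ-5D-5L at T0_1, T3 and T4 (Table 1).
- 12-month horizon (Cost-effectiveness).
- 100 per arm (Design).

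**Assumptions, not in the article**
- Trapezoid AUC with waves at about 0, 6 and 12 months.
- Equal utility SD at each wave, 0.20-0.30.
- A common between-wave correlation r of 0.4-0.6.
- Complete data on 100 per arm.

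**Step 1: AUC weights.** Each six-month interval contributes half a year times the mean of its two end points. The weights are 0.25 (T0_1), 0.50 (T3) and 0.25 (T4).

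**Step 2: pass-through of a baseline imbalance.** The slope of QALY on baseline utility is 0.25 + (0.50 + 0.25)r = 0.25 + 0.75r.

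**Step 3: share of QALY variance explained by baseline.** In units of SD², the QALY variance is 0.25² + 0.50² + 0.25² + 2r(0.125 + 0.0625 + 0.125) = 0.375 + 0.625r. The explained share is the slope squared divided by this variance.

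| r | slope | QALY variance / SD² | variance removed by adjustment |
|---|---|---|---|
| 0.4 | 0.55 | 0.625 | 0.3025 / 0.625 = 48% |
| 0.5 | 0.625 | 0.6875 | 0.3906 / 0.6875 = 57% |
| 0.6 | 0.70 | 0.75 | 0.49 / 0.75 = 65% |

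Neither the pass-through nor the variance reduction depends on the assumed SD or on the number per arm.

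**Step 4: size in QALYs.** The SE of the baseline difference is SD × √(2/100), which is 0.028 at SD 0.20 and 0.042 at SD 0.30. A one-SE imbalance shifts the unadjusted QALY difference by 0.55 × 0.028 = 0.016 at the low end and 0.70 × 0.042 = 0.030 at the high end.

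**Step 5: the same shift against the estimate's own SE.** The ratio is the square root of the explained share: √0.484 = 0.70 to √0.653 = 0.81. A one-SE baseline imbalance therefore moves the unadjusted QALY difference by 0.70-0.81 of its own SE, whatever the SD.

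**Step 6: one case in full, SD 0.25 and r = 0.5.**
- The SE of the baseline difference is 0.25 × √0.02 = 0.035.
- The unadjusted SE of the QALY difference is 0.0354 × √0.6875 = 0.029.
- The adjusted SE is 0.0293 × √(1 − 0.568) = 0.019.
- A one-SE imbalance shifts the QALY difference by 0.625 × 0.0354 = 0.022. Of this, 0.25 × 0.0354 = 0.009 comes from the baseline weight alone, and the rest from carry-over to T3 and T4.

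A simulation of this case (20,000 replicates, no treatment effect) gave SEs of 0.029 and 0.019. The slope on the baseline imbalance was 0.63 unadjusted and 0.00 adjusted. The mean error was about 0 for both estimators.

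**Sensitivity to the assumptions**
- With SD 0.15-0.30 and r 0.3-0.7, pass-through runs from 48% to 78%, a one-SE shift from 0.010 to 0.033 QALY, and the variance reduction from 40% to 74%.
- With 95 per arm, the SEs in the case above become 0.030 and 0.020.
- T3 is counted from the start of TAU, and screening is preferably one to four weeks earlier, so T3 can fall up to about a month later than month 6 from baseline. At month 7 the baseline weight is 7/24 = 0.29 and the slope is 0.29 + 0.71r, or 0.58-0.72 for r 0.4-0.6. The six-month approximation does not inflate the result.

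**The case against.** The strongest objection is that an unadjusted main analysis is inferred, not stated. The AUC sentence defines how one patient's QALY is computed, which is also the first step of a baseline-adjusted regression. The article does not say how the incremental QALY is estimated, and the full covariate set is commonly left to a fuller protocol or an economic analysis plan. This stands in part. A reader might take the article to say that raw AUC means are compared, but those words are not there. What remains is that the article does address covariate adjustment and makes it a sensitivity analysis of the CEACs. That placement is a choice, and its natural implication is an unadjusted main result.

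Second, net benefit contains the QALY, so the planned net benefit regression could include baseline utility. That is true, and it would help the adjusted CEACs. It would leave the main ICER and the cost-effectiveness plane as they are, and nothing commits it to that covariate.

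Third, a reader might infer that the main ICER is biased or invalid, or that a baseline difference passes into it one for one. Neither follows. Under randomisation the unadjusted difference is unbiased on average, the bootstrap already shows chance imbalance as uncertainty, and pass-through is partial.

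Fourth, a reader might conclude that the artefact rivals the true QALY gain or would reverse its sign. The article gives no expected gain, so this cannot be judged.

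**Conclusion.** The point holds as an analysis choice worth changing; it does not invalidate the economic evaluation. By placing adjustment only in a CEAC sensitivity analysis with unnamed covariates, the article implies a main incremental QALY, ICER and bootstrap without adjustment for T0_1 utility.

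The loss has two parts: bias conditional on whatever imbalance the realised trial has, and precision given away. The estimates are a pass-through of about 55-70% and a possible variance reduction of about 48-65%. They rest on waves near 0, 6 and 12 months, equal SDs and a common between-wave correlation of 0.4-0.6. The shifts in QALY units also rest on an assumed SD of 0.20-0.30 and 100 per arm. None of the SD or correlation values comes from the article.

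The check covers baseline utility only. It gives no basis for also requiring adjustment for site or for baseline costs.

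**What to change.** In the main cost-utility analysis, estimate the incremental QALY by regressing 12-month QALYs on arm and T0_1 EQ-5D-5L utility within each bootstrap sample, and use that estimate for the ICER, the plane and the CEAC. Report the unadjusted AUC difference as a sensitivity analysis. If a fuller plan already does this, one sentence saying so settles the point.

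The cost is one sentence in the plan and one regression per bootstrap replicate. Baseline utility is already collected, so no new data, visits or patients are needed.
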